#### Statistical analyses

Data management and statistical analyses will be carried out using SAS version 9.4 software (SAS Institute Inc., Cary, NC, USA) and STATA version 16 (StataCorp LLC, Texas, USA). The analyses will be supplemented by modelling and graphics using “R” software (Version 3.6.1) [25].

Data analyses will be conducted according to intention-to-treat principles and include all eligible patients with available outcome data. The analyses will be conducted according to the randomization schedule. Citizens’ characteristics will be reported using numbers/percentages, means (SD), and medians [IQR]. Differences between the intervention and control groups will be calculated using chi2 tests, Student’s t-test, or Kruskal-Wallis test, as appropriate. The statistical significance threshold for all tests will be set to *P* < 0.05.

When presenting the results of our study we will use suiting EQUATOR network guidelines such as the CONSORT 2010 statement [40] with the extension for stepped wedge cluster randomized trials [41].

#### Analysis of primary and secondary outcomes

Outcomes are shown in Table 2. The primary outcome, proportion of acute admission, will be analyzed using co-variance, repeated measure analysis and logistic regression. A key event is the switch from the usual care to intervention phase. We will treat the intervention regression coefficient as a slopes term to account for potential differences in intervention effects across area home care teams. The analyses will be adjusted for relevant confounders such as age, gender, co-morbidity, functional level and frailty.

For secondary outcomes (Table 2) 2, 3, 4, 5 and 6 we will use logistic regression to analyze occurrence of event. Citizens, who relocate to another municipality, move into a care home, or die during the study period will be excluded from the analyses. Models for acute admission will be used and the incidence of acute admission will be analyzed using logistic regression. The analysis will be adjusted for confounding factors such as age, gender and co-morbidity. We will stratify the analyses by municipalities and area home care teams to control for differences between these.

When analyzing readmission between the intervention and control group we will focus on both the 30-day readmission rate (outcome 3) and 90-day readmission rate (outcome 4). The index-admission will be defined as any admission to a Danish hospital during the study period. Citizens with multiple hospital admissions can have several index admissions but only one readmission per index admission.

Changes in citizens health service utilization (outcome 7, 8 and 9) will be evaluated in order to assess changes in costs of care and treatment in the primary and secondary health care sector. We will analyze the average cost per citizen, as well as analyses of the change in costs in primary and secondary health care. We will also analyze the costs of implementing the PATINA algorithm and decision support tool (outcome 10). This will be done by summing up the time spent on project related activities by both nurses and project coordinators in each municipality. The costs of implementing the algorithm will be reported as the total cost of the intervention with a 95% confidence interval.

Barriers and facilitators for nurses’ acceptance and use of the algorithm (outcome 11) will be analyzed using data gathered in a three-wave survey, which will be integrated in SW-RCT design and follow the step-wise implementation of the algorithm in each of the tree municipalities. When an area home care team is randomized to the intervention group the nurses allocated the section will complete a survey on three occasions; before the algorithm is implemented, just after having received training in the use of the algorithm, and after having worked with the algorithm for one month. The survey consists of several validated item scales within the areas of change management, motivation approach, intrinsic motivation, basic need satisfaction, public service motivation, technology acceptance and relational coordination. The analysis will aim to investigate the role of public professionals in achieving the desired effects of implementing algorithms in areas of public health administration and contributes to the broader public management and change management literature, by linking employees’ motivation and attitudes toward a change to the outcome of that change.

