#### PATINA algorithm

The algorithm monitors and analyzes community-dwelling older citizens’ use of municipal home and nursing care with almost real time data (one-week delay). It uses individual administrative data on assigned amount of time (minutes per week) for home care, practical (domestic) help, training/rehabilitation, and nursing care delivered to each citizen.

In each of the three municipalities, a weekly data set with information on health care use during the past week is fed into three separate secure databases via a front-end upload module. Data is then analyzed by the algorithm by comparing home care utilization the last month to a prior period of six months. The algorithm then produces a list of citizens that have triggered the threshold configured for the algorithm. A graph visualizing each citizens utilization of personal care, practical help, training/rehabilitation and nursing care during the last six months is also produced, see Fig. 2.

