**Fig. 2 Fig2:**
[figure not shown]
Graph from the PATINA algorithm visualizing a citizen’s utilization of home care (practical help and personnel care), nursing, training and total help

In the intervention phase, nurses in the included area home care teams receive the list of citizens that have surpassed the threshold. These are considered to be at increased risk of adverse health outcomes and subsequently of acute hospitalization. The list also provides graphs visualizing each citizens’ health service utilization. Simultaneously, the algorithm sends the information to a research database setup in Redcap [31, 32], which then forwards a unique link for each citizen to an allocated community nurse. The link gives the nurse access to the ‘PATINA decision support tool’. The tool is designed as a questionnaire, which is covered and filled-in by the nurse.

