#### PATINA decision support tool

The PATINA decision support tool is designed to nudge nurses to reflect upon more recent notifications in the electronic care records regarding changes in health and need of care. Such changes may be subtle signs of health deterioration, and not just ageing processes. Additionally, the ‘PATINA decision tool’ includes validated health assessment scales and information on risk factors of acute disease, such as functional level (Barthel-20) [33], frailty (Clinical Frailty Scale) [34, 35], Brief Geriatric Assessment [36], medications, falls tendency, weight, mental state, dehydration, and more. Further, the tool supports and covers areas of health care, which nurses in Denmark are obligated to assess regularly, e.g. assessment of citizens general state of health [37].

Nurses complete the decision support workflow by reviewing information in the citizen’s electronic care record and apply their knowledge about the citizen from their daily work. After assessing a ‘citizen at risk’ using the decision support tool, the data is sent to the research database and a PDF file containing the assessment is automatically forwarded to the nurse via email. The PDF file is then saved on the citizen’s electronic health record for later use by the nurse and other colleagues, as well as for reference.

Data from the citizen can trigger the algorithm’s alarm for several weeks in a row. The first time a citizen appears on the list the nurse must assess the citizen’s current health and functional situation using the PATINA decision support tool. When a citizen continues to be on the list, the nurse compares the citizens actual health care situation with the latest ‘PATINA decision tool assessment’, thereby judging whether the citizen’s situation has worsened, and further action is needed. In this case the citizen is assessed once more using the decision tool and a PDF file is saved as a new reference point.

The IT ecosystem and data flow of the project are visualized in Fig. 3. A more detailed description of how the algorithm has been developed, IT infrastructure and security, and how the threshold was configured, will be presented later in a separate paper.

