#### Data collection

Data will be collected continuously on a weekly basis during the course of the study. In a typical week nurses in an intervention area home care team each receive a list of citizens at risk on a Monday morning. The nurses have two days (until Wednesday) to assess each citizen’s health situation using the ‘PATINA decision support tool’. On the fourth day (Thursday), the project manager (AF) carries out a weekly quality assessment of the gathered data. If data is missing or major errors are identified the project coordinator contacts the nurse responsible for the entered data to discuss the case, and if needed, adjust accordingly.

In accordance with Danish laws on data protection study data will be collected and stored in REDCap (version: REDCap 9.1.15 -© 2020 Vanderbilt University) [31, 32], an electronic data capture tool hosted at OPEN at Odense University Hospital, the Region of Southern Denmark. Data from the PATINA algorithm and decision support tool will be linked to data from Danish national health registries using the citizens unique social security number. The registers include data from the National Patient Registry (history of disease, diagnosis, acute or elective admissions, readmissions, outpatient care and hospital treatment), the National Health Insurance Service Register (services from primary care physicians, the Register of Medicinal Product Statistics, and the Danish Civil Registration System (age, gender, marital status and more).

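### The primary analysis names functional level and frailty as adjusters, but the only source described is the decision support tool, used only in the intervention phase; with tool scores in the model, the intervention effect is not identified

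*Protocol article*

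**What the plan says.** All references are to the Protocol article.

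- **Adjustment set.** Analysis of primary and secondary outcomes, in the paragraph on the primary outcome: "The analyses will be adjusted for relevant confounders such as age, gender, co-morbidity, functional level and frailty".
- **Where the two variables are measured.** The section PATINA decision support tool lists among the tool's contents "functional level (Barthel-20) [33], frailty (Clinical Frailty Scale) [34, 35], Brief Geriatric Assessment [36".
- **When and by whom the tool is used.** The section PATINA algorithm (text after Fig. 2) says: "In the intervention phase, nurses in the included area home care teams receive the list of citizens that have surpassed the threshold". At the same time the research database "forwards a unique link for each citizen to an allocated community nurse", and that link opens the tool. Data collection confirms the setting: "In a typical week nurses in an intervention area home care team each receive a list of citizens at risk on a Monday morning".
- **What is available in both phases.** Of the algorithm feed, the section PATINA algorithm says: "It uses individual administrative data on assigned amount of time (minutes per week) for home care, practical (domestic) help, training/rehabilitation, and nursing care". Data collection adds the linked registers: disease history and admissions from the patient registry, primary care services, medicines, and "the Danish Civil Registration System (age, gender, marital status and more". Neither functional level nor frailty is listed for any of these sources.
- **A second adjustment list.** The following paragraph of the analysis section, mainly on secondary outcomes, also mentions logistic regression for the incidence of acute admission. Its list of adjusters stops at age, gender and co-morbidity.

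**The concern.** An adjuster in a stepped-wedge comparison has to be observed on both sides of the crossover and should not be produced by the intervention. On the sources described, functional level and frailty meet neither condition. They come from a questionnaire that nurses open because a citizen was flagged in a team already using the intervention.

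If the analyst puts those scores into the primary model, there is no control-phase information to compare with. The usual ways out do not help. Deleting incomplete records removes the control phase. A missing-value indicator duplicates the intervention term. Imputing control-phase scores from intervention-phase data assumes that the scores relate to the other variables in the same way in both phases. No data can check this, so the imputed score cannot correct a real difference in frailty between the phases. The scores are also assigned by unblinded nurses as part of the intervention, so they are not baseline confounders in the ordinary sense.

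The practical risk is that the named primary adjustment proves impossible once the data are assembled, and the covariates are then chosen with the outcome data in view.

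**Working it through.** The plan states no figure on this point, so there is none to reproduce. The check has three steps.

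**1. Source of each covariate by phase, from the sections cited above**

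| Covariate | Source described | Control phase | Intervention phase |
|---|---|---|---|
| Age, gender | Civil registration | yes | yes |
| Co-morbidity | Disease history, patient registry | yes | yes |
| Weekly care minutes | Algorithm feed | yes | yes |
| Functional level | Barthel-20 in the tool | none described | flagged citizens |
| Frailty | Clinical Frailty Scale in the tool | none described | flagged citizens |

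**2. Can the intervention effect be identified?**

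Inputs from the article: 20 teams (3, 7 and 10), a new team every 12, 6 and 4 weeks, and a one-year intervention period. Assumptions: 13 four-week periods, the first crossover one step after the start, and 4,000 simulated rows (the rank result does not depend on this number).

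Columns: intercept 1 + intervention 1 + periods 12 + teams 19 = 33. One tool score makes 34, and a missing-value indicator makes 35.

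| Model | Rows kept | Control rows | Columns | Rank | Effect identified |
|---|---|---|---|---|---|
| Score known in both phases (hypothetical) | 4,000 | all | 34 | 34 | yes |
| Tool score, complete cases | 2,202 | 0 | 34 | 32 | no |
| Tool score plus missing indicator | 4,000 | all | 35 | 34 | no |
| No tool score | 4,000 | all | 33 | 33 | yes |

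In the complete-case model the intervention column X equals 1 in every remaining row, so its variance is 0 and it cannot be separated from the intercept. That is one lost rank. The second arises because, on this schedule, the first period has no intervention rows, so the 12 period columns sum to the intercept. With the missing indicator M, M = 1 − X; its correlation with X is −1 and X + M equals the intercept. These are properties of the linear predictor, so they hold for logistic regression too. Letting the effect vary by team, as the plan intends, does not restore the missing contrast.

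**3. How much of the trial is control time?**

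Control share of a municipality = mean crossover week / 52, pooled with the populations above 65 years in Table 1 (6,142, 14,206 and 35,811; total 56,159).

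- First crossover at week 0: Kerteminde (0, 12, 24) 12/52 = 23%; Svendborg (0 to 36) 18/52 = 35%; Odense (0 to 36) 18/52 = 35%. Pooled: (6,142 × 12 + 50,017 × 18) / (56,159 × 52) = 33%.
- First crossover one step in: 24/52 = 46%, 24/52 = 46% and 22/52 = 42%. Pooled: (20,348 × 24 + 35,811 × 22) / (56,159 × 52) = 44%.

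This is a share of team-time. The primary outcome concerns flagged citizens, and the article does not give their split by phase. The figure shows how much would be lost; the identification result does not depend on it.

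**The case against.** A reader might infer that functional level and frailty exist nowhere in the control phase, and that the trial therefore cannot produce an adjusted effect. The article does not support this, for four reasons.

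- **The tool as sole source is an inference.** The analysis section names concepts, not the two scales. Setting and study population says that municipal services are allocated according to functional level. The tool section says that nurses consult the electronic care record and that the tool covers areas they must assess regularly in any case. Functional information may therefore exist in usual care. This stands. However, the article plans no extraction of it and mentions nothing comparable for frailty.
- **The list is illustrative.** It is open-ended, and an article may leave operational detail to a fuller document. This also stands in part. But both variables are expressly named for the primary outcome, while the second list omits them. The difficulty is a named covariate that does not fit the named sources, not an absent detail.
- **Complete-case analysis is not stated.** Correct: the analysis set is defined by available outcome data. That definition itself sits badly with a model that would drop every control record, and the missing-indicator route fails as well. The failure would be visible to the analyst, so it is unlikely to pass as a silent bias.
- **The scores are taken close to the flag.** Nurses have until Wednesday after the Monday list, so at a first flag little care would have changed beforehand. This limits how far intervention effects could have altered the score, and the size of any such bias is unknown. It does not supply control-phase values.

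A citizen flagged in the control phase and again after crossover would have a later score. That score is recorded under the intervention and exists only for those who stayed and were flagged again, so carrying it back is no remedy.

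**Conclusion.** The point holds conditionally. If the tool's Barthel-20 and Clinical Frailty Scale scores are the intended covariates, all control-phase values are missing and a primary model that includes them cannot identify the intervention effect under complete-case or missing-indicator handling. The values that exist are recorded after crossover as part of the intervention.

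The defect is confined to two covariates. Models with age, gender and register co-morbidity are estimable, and the article already lists that set in connection with acute admission. The conclusion rests on two assumptions: that the tool is the source, since none other is described, and that the tool is not completed in control-phase teams, as the description of the intervention phase implies.

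**What to change.** In the primary-outcome paragraph, limit adjustment to covariates obtained the same way in both phases and before the flag: age, gender and register co-morbidity. Optionally add home-care and nursing minutes from the algorithm's six-month reference period, as a proxy for function that is already collected. Report the tool's Barthel and frailty scores only to describe intervention-phase citizens. Keep functional level or frailty as adjusters only if the plan names a pre-flag source that covers both phases.

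Cost: a wording change to the analysis section and any analysis plan. All the replacement covariates are already in the data feed or the linked registers. The small downside is less direct adjustment for frailty.

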The primary objective of the PATINA project is to implement and evaluate the combined effect of the ‘PATINA algorithm and the decision support tool’ on the prevention of acute hospital admissions of older community-dwelling citizens [3]. Further, we will evaluate the effects on citizens utilization of health care service in the primary and secondary health care sector and estimate costs. A second objective is to investigate nurses’ role in achieving the desired effects of the implementation, by linking employees’ motivation and attitudes toward the ‘PATINA algorithm and the decision support tool’ to the primary and secondary outcome of the study.

In this paper, we present the study protocol for the PATINA project, where we use a stepped-wedge randomized controlled trial, explaining the methods, design and intervention of the study. The study protocol (version 1.2, 13 May 2020) follows the SPIRIT statement [26] and has been adapted to suit the format of an article.

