***Secondary outcomes***		
Outcome 2	Preventable admission	Preventable admission after being identified at risk by the algorithm
Outcome 3	Readmission (30-days)	Readmission to a Danish hospital within 30 days from a hospital discharge
Outcome 4	Outpatient contacts	Proportion of contacts to outpatient clinics after being identified at risk by the algorithm
Outcome 5	Primary care physicians contacted	Contacts to a primary care physician after being identified at risk by the algorithm
Outcome 6	Death (90-days)	Proportion of diseased citizens identified at risk by the algorithm within 90 days

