***Health care utilization and economic outcomes***		
Outcome 7	Changes in utilization and costs of municipal home, nursing and social care services	Information on municipal home, nursing and social care services will be collected as part of the data used in the PATINA algorithm. Costs will be summed from the first date a citizen is identified at risk by the algorithm
Outcome 8	Changes in utilization and costs of planned and unplanned hospital treatment	Information on hospital treatment (planned and unplanned) will be collected from the Danish National Patient Registry. Costs will be summed from the first date a citizen is identified at risk by the algorithm
Outcome 9	Changes in utilization and costs of contacts to primary care physicians	Information on contacts to primary care physicians will be collected from the Danish National Health Insurance Service Register. Costs will be summed from the first date a citizen is identified at risk by the algorithm
Outcome 10	Cost of implementation of the PATINA algorithm and decision support tool	The cost of implementing the algorithm and decision support tool will be calculated as time total time spent for introduction and working with the algorithm for each nurse

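### Primary care physician contacts (outcome 5) recur, but are analysed only as any contact versus none, and no other planned analysis directly estimates contact frequency

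*Protocol article*

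**What the plan says.** The section on analysis of primary and secondary outcomes sets one rule for five outcomes, numbers 2 to 6 of Table 2: "we will use logistic regression to analyze occurrence of event". The list puts death, which happens once, under the same binary rule as physician contacts, which can recur.

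Table 2 gives the measure for outcome 5 as "Contacts to a primary care physician after being identified at risk by the algorithm". For outcome 4 it gives "Proportion of contacts to outpatient clinics after being identified at risk by the algorithm". The analysis section, however, also uses that number for a different quantity: "90-day readmission rate (outcome 4)".

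The Background says that "we will evaluate the effects on citizens utilization of health care service" in both care sectors. A separate block of Table 2 on utilisation and economic outcomes lists outcome 9, "Changes in utilization and costs of contacts to primary care physicians", and outcome 8, "Changes in utilization and costs of planned and unplanned hospital treatment". The analysis section evaluates outcomes 7 to 9 for the purpose of assessing costs. It names average cost per citizen and change in costs, and no count or rate model.

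**The concern.** An occurrence analysis gives a citizen with one physician contact and a citizen with ten the same value. If the intervention changes how often flagged citizens see their physician, rather than whether they see one at all, most of that change lies where the binary outcome cannot register it. The flagged group consists of home-care recipients in the 65-plus age range whose care use has just risen, so repeat contacts are plausible.

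At stake is a secondary result. A null finding for any contact could be taken as no change in physician use when the number of contacts had changed. The article names the National Health Insurance Service Register as the source for primary care physician services, so the count should be obtainable without new data collection.

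**Working it through.** **No plan figure to reproduce.** The article gives no contact rate, dispersion, effect size or power for outcome 5. Its only power statement concerns acute admission. Everything below is an illustration on assumed inputs, shown as a range.

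**1. Information kept by any/none.** Let the number of contacts per citizen have mean m and variance m + k·m² (Poisson when k = 0, negative binomial when k > 0).

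- Probability of any contact: P = 1 − (1 + k·m)^(−1/k), or 1 − e^(−m) when k = 0.
- Information per citizen on log m from the count: 1 / (1/m + k).
- Information per citizen on log m from any/none: (dP/d log m)² / [P(1 − P)], where dP/d log m = m(1 + k·m)^(−1/k − 1), or m·e^(−m) when k = 0.
- Share kept = second divided by first.

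Worked case, m = 1 and k = 1: P = 1 − 1/2 = 0.5; dP/d log m = 1 × 2^(−2) = 0.25; any/none information = 0.0625 / 0.25 = 0.25; count information = 1/2 = 0.5; share kept = 50%.

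| Mean contacts m | Share kept, k from 0 to 2 |
|---|---|
| 0.3 | 71-86% |
| 0.5 | 60-77% |
| 1 | 45-58% |
| 2 | 31-33% |
| 3 | 16-26% |
| 4 | 7-22% |
| 10 | 0-13% |

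**2. What this means for power, example A.** Assume m = 3, k = 1, a true rate ratio of 0.85, 1,000 citizens per phase, two-sided 5%, no allowance for clustering or time.

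- Count: means 3 and 2.55. SE of the log rate ratio = √[(1/3 + 1 + 1/2.55 + 1)/1000] = 0.0522. |log 0.85| = 0.1625. z = 0.1625/0.0522 = 3.11. Power = Φ(3.11 − 1.96) = 0.88.
- Any/none: P = 3/4 = 0.750 and 2.55/3.55 = 0.718. The odds are 3 and 2.55, so the absolute log odds ratio is again 0.1625. SE = √[(1/(0.750 × 0.250) + 1/(0.718 × 0.282))/1000] = 0.1014. z = 1.60. Power = Φ(1.60 − 1.96) = 0.36.
- Ratio of squared z: (1.603/3.113)² = 0.27, in line with the table.

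**3. Example B, other assumptions.** Take the midpoint of the stated population of 5,500 to 6,000, which is 5,750, or 2,875 per condition, with k = 1 and a rate ratio of 0.9. Power for count against any/none is 0.80 against 0.51 at m = 1, 0.94 against 0.37 at m = 4, and 0.97 against 0.22 at m = 10. At m = 0.3 it is 0.47 against 0.38. The whole population will not be flagged, so these sample sizes are for scale only.

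**4. Does another outcome fill the gap?** Outcome 9 covers use of physician contacts, from the same register. Its stated analysis is in costs. A cost difference mixes the number of contacts with their price, so it is not a direct estimate of contact frequency.

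**The case against.** The strongest reply has four parts.

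- **Amount of use is not ignored.** Outcome 9 addresses physician contacts and outcome 8 hospital treatment. A reader might infer that the plan throws utilisation away; it does not. What stands is narrower: the stated analysis of these outcomes runs through costs, no count or rate analysis is named, and outcome 8 does not name outpatient contacts.
- **Outcome 4 is not defined as a count.** A reader might infer that both contact outcomes are counts wrongly dichotomised. Table 2 words outcome 4 as a proportion, which logistic regression may suit, and the analysis section gives the same number to 90-day readmission. This part of the reply stands: what outcome 4 is comes before how to model it.
- **The size of the loss is unknown.** If contacts are rare, as they may be over a short window, any/none keeps most of the information. The article states no window for outcome 5. Nor is a ceiling shown: in example A the any-contact proportion falls from 75.0% to 71.8%, well short of saturation. This also stands, and it makes the size conditional.
- **Any contact versus none is a legitimate question for a secondary outcome.** True. No bias or invalid test is shown.

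What survives is that, for a recurrent event, the stated method answers a narrower question, and with less power than a count model in every scenario of example B.

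**Conclusion.** The point holds for outcome 5 and is conditional for outcome 4. The stated analysis of outcome 5 does not measure how often citizens contact their physician, and no other stated analysis estimates that directly.

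The cost in information is small to moderate if contacts are rare (70-85% kept at a mean of 0.3), about half at a mean of 1, and three quarters or more at means of 3-4 and above. These figures rest on assumed Poisson or negative binomial counts with dispersion 0 to 2, and on independent citizens without cluster or period effects. Absolute power in the trial would differ.

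The documents do not support calling the logistic analysis an error of inference, or stating as fact that much of the information is lost, because they give no contact rates. This is a worthwhile and cheap improvement to a secondary analysis.

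**What to change.** - **Outcome 5.** State that the measure is the number of primary care physician contacts after the flag, and over what follow-up. Analyse it with a mixed-effects negative binomial (or similar rate) model, with log person-time after the flag as offset and the same team and calendar-period terms as the primary model. Report a rate ratio with its confidence interval, and keep any/none as a supportive analysis.
- **Outcome 4.** Reconcile Table 2 with the analysis section so that the number refers to one outcome only. If it is outpatient contacts, say whether the measure is any contact or the number of contacts. If the number, use the same model as for outcome 5.

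The cost is a change of wording in the analysis plan, since the register linkage is already planned. The small downside is a distributional assumption and a rate ratio in place of an odds ratio.
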